## Abstract

Hyperlactatemia occurs frequently after brain tumor surgery. Existing studies are scarce and predominantly retrospective, reporting inconsistent associations to new neurological deficits and prolonged hospital stay. Here we describe a protocol for a prospective observational study of hyperlactatemia during and after elective tumor craniotomy and the association with postoperative outcome, as well as selected pathophysiological aspects, and possible risk factors. We will include 450 brain tumor patients scheduled for elective craniotomy. Arterial blood samples for lactate and glucose measurement will be withdrawn hourly during surgery and until six hours postoperatively. To further explore the association of hyperlactatemia with perioperative insulin resistance, additional blood sampling measuring markers of insulin resistance will be done in 100 patients. Furthermore, in a subgroup of 20 patients, blood from a jugular bulb catheter will be drawn simultaneously with blood from the radial artery to measure the arterial to jugular venous concentration difference of lactate, in order to study the direction of cerebrovascular lactate flux. Functional clinical outcome will be determined by the modified Rankin Scale, length of stay and mortality at 30 days, 6 months, 1 year and 5 years. Clinical outcome will be compared between patients with and without hyperlactatemia. Multivariate logistic regression will be used to identify risk factors for hyperlactatemia. A statistical analysis plan will be publicized to support transparency and reproducibility. Results will be published in a peer-reviewed journal and presented at international conferences.

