### Hyperlactatemia in brain tumor surgery: Pathophysiological implications

The cause of hyperlactatemia in brain tumor surgery is debated. Both tumor characteristics [10, 12–14], comorbidity [15], perioperative rhabdomyolysis [16], length of surgery [7], and type of anesthesia [17] have been suggested to play a part.

Lactate is well-known as a marker of global or regional ischemia, but as an additional consideration hyperlactatemia is also a marker of increased non-oxidative glycolysis and may be induced by hyperglycemia in healthy subjects [18]. Insulin resistance is a common side effect of glucocorticoid treatment and can also be induced in healthy subjects after short-term treatment [19]. As the majority of patients undergoing tumor craniotomy are treated with glucocorticoids either preoperatively (especially prednisolone to reduce edema and thus intracranial pressure), intraoperatively (especially dexamethasone, to reduce the perioperative stress response) or both, glucocorticoid-associated insulin resistance is an attractive explanation of hyperlactatemia after tumor craniotomy.

Lactate has previously been shown to act as a substrate for the brain in conditions with hyperlactatemia such as physical activity or lactate infusion [20]. It is therefore likely that perioperative hyperlactatemia associated with tumor craniotomy is also associated with increased cerebral lactate metabolism and, therefore, a net cerebrovascular lactate influx (i.e., a positive arterial to jugular venous concentration difference). This has never been addressed and would contrast with the usual finding of a slight net cerebrovascular lactate outflux from the brain to the bloodstream (i.e., a negative arterial to jugular venous concentration difference) at normal serum lactate.

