The present research protocol describes a prospective study consisting of four sub-studies to further explore hyperlactatemia in tumor craniotomy patients. We intend to investigate whether hyperlactatemia is related to clinical outcome (sub-study I) and identify possible risk factors associated with hyperlactatemia (sub-study II). In subsets of patients, we aim to study whether hyperlactatemia in this context is associated with pre- and postoperative insulin resistance (sub-study III) as well as a net cerebrovascular influx of lactate (sub-study IV). We hypothesize that tumor size, preoperative glucocorticoid dose and the severity of hyperlactatemia is associated to functional clinical outcome, with preoperative glucocorticoid dose as the independent risk factor. Furthermore, we expect the severity of insulin resistance and hyperglycemia to be associated with the severity of hyperlactatemia, and that hyperlactatemia is associated with a net cerebrovascular influx of lactate.

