### Definitions and calculations

Hyperlactatemia is defined as the measurement of at least one value of S-lactate > 2.2 mmol / L during the observation period starting at surgical incision and ending after 6-hours of observation in the Post Anesthesia Recovery Unit.

Peak lactate is defined as the highest value of S-lactate measured during the observation period.

Mean S-lactate is calculated as the area under the curve for S-lactate over time during the observation period, divided by the duration in hours. This is calculated to estimate the “total” lactate load regardless of whether the triggers occur pre-, intra- or postoperatively.

Intra- / postoperative lactate excess is calculated as mean S-lactate minus S-lactate at surgical incision. This is calculated to estimate the "pure" perioperative contribution to the lactate load.

Arterio-venous concentration difference (a-jD) for lactate, glucose, and oxygen: the concentration in jugular bulb blood minus the concentration in arterial blood.

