### Study endpoints

#### Primary endpoints

Sub-study I: Change in mRS from preoperative assessment to 30 days after surgery, in patients with and without hyperlactatemia.

Sub-study II: Prevalence of hyperlactatemia (defined as at least one measurement of S-lactate> 2.2 mmol / L).

Sub-study III: Association between preoperative and/or intraoperative glucocorticoid treatment, HbA1c and pre-/ postoperative insulin resistance (measured by HOMA-IR), adjusted for hours after surgery.

Sub-study IV: Perioperative change in a-jD (lactate) corrected for change in a-jD (O_2_) from first to last measurement.

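### Sub-study IV: the a-jD formula (jugular minus arterial) has the opposite sign to its own name and to the influx/outflux convention in the Introduction

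*Protocol article*

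**What the plan says.** The Introduction (section on pathophysiological implications) ties sign to direction twice. Uptake by the brain is "a net cerebrovascular lactate influx (i.e., a positive arterial to jugular venous concentration difference"), and the usual state at normal lactate is a slight "net cerebrovascular lactate outflux from the brain to the bloodstream (i.e., a negative arterial to jugular venous concentration difference"). The Introduction's closing paragraph states the hypothesis that "hyperlactatemia is associated with a net cerebrovascular influx of lactate". The Abstract gives the purpose of the paired sampling in 20 patients: "in order to study the direction of cerebrovascular lactate flux".

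Definitions and calculations then names the variable "Arterio-venous concentration difference (a-jD) for lactate, glucose, and oxygen" and gives its formula as "the concentration in jugular bulb blood minus the concentration in arterial blood".

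Under Primary endpoints, the sub-study IV endpoint is built on this variable: "Perioperative change in a-jD (lactate) corrected for change in a-jD (O_2_) from first to last measurement".

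**The concern.** The formula subtracts in the opposite order to the one that the Introduction interprets, and to the one that the variable's name implies. No part of the article states a reversed convention, such as negative meaning uptake, that would bring the two into line.

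Sub-study IV asks a directional question, so the sign carries much of the answer. Two analysts could each follow the article faithfully, one from the formula and one from the Introduction, and obtain values of opposite sign from the same samples. If the formula supplies the number and the Introduction supplies its meaning, a result that supports the hypothesis reads as one that contradicts it. The same formula governs oxygen, which is the correcting term in the primary endpoint, and glucose.

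**Working it through.** There is no plan figure to reproduce, because the article gives no a-jD values. The check is algebraic. The concentrations below are assumptions chosen only to show the signs.

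**Definitions**
- Introduction: D = a - j, with D > 0 for influx and D < 0 for outflux.
- Definitions and calculations: D* = j - a.
- Therefore D* = -D for any pair of concentrations. Every nonzero value changes sign, and its size does not change.

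**Single time points (assumed, mmol/L)**

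| State | a | j | a - j | j - a | Literal value read with the Introduction |
|---|---|---|---|---|---|
| Net uptake | 3.0 | 2.8 | +0.20 | -0.20 | outflux |
| Net outflux | 1.0 | 1.1 | -0.10 | +0.10 | influx |

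**Change from first to last measurement, for a patient moving from the outflux row to the uptake row**
- With a - j: (+0.20) - (-0.10) = +0.30.
- With j - a: (-0.20) - (+0.10) = -0.30.

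**The oxygen correction.** The endpoint does not say what form the correction takes, so the effect has to be followed for each plausible form. Assume an arterial-minus-jugular oxygen difference of 3.0 at the first measurement and 2.5 at the last. Under the literal formula these become -3.0 and -2.5.

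1. *No correction (lactate difference alone).* The sign is reversed, as above.
2. *Regression adjustment.* Write the model as ΔL = α + β·ΔO2. With both variables reversed, -ΔL = α* + β*·(-ΔO2), which gives β* = β and α* = -α. The slope is unchanged, but the adjusted mean change is reversed.
3. *Lactate/oxygen ratio at each time, then the change.*
   - With a - j: 0.20/2.5 - (-0.10)/3.0 = 0.080 + 0.033 = +0.113.
   - With j - a: (-0.20)/(-2.5) - (0.10)/(-3.0) = 0.080 + 0.033 = +0.113.
   - The two reversals cancel.
4. *Ratio of the two changes.* +0.30/(2.5 - 3.0) = -0.60, and -0.30/(-2.5 + 3.0) = -0.60. The reversals cancel here too.

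**Inference.** Multiplying a variable by -1 leaves its standard error and the absolute value of its test statistic unchanged. Two-sided p-values for the lactate difference are therefore the same under either definition. Only the stated direction differs.

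**The case against.** The strongest reply is that this is a slip in one clause that anyone can detect. The Abstract, the Introduction and the variable's own name all point to arterial minus jugular. Literal coding would also give a negative oxygen difference for a brain that consumes oxygen, which is a visible warning in the same dataset. An analyst who codes the formula literally and reads negative as uptake reaches the right conclusion, and so does one who codes by the name. Only the mixed case misleads. The samples are stored as separate arterial and jugular values, so the sign can be corrected at any time. Only 20 of the 450 patients are involved, and the endpoints of sub-studies I to III do not use a-jD.

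All of this stands as a limit on the consequence. It does not remove the contradiction: the section that fixes the calculation gives the opposite sign to the section that fixes the interpretation.

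A reader might infer that sub-study IV will report uptake as efflux, or that its primary result is bound to be completely reversed. The article does not support either reading:
- Misreporting requires the literal formula and the Introduction's convention to be combined without anyone noticing.
- The endpoint is a corrected change, not the sign at one time. A change toward uptake can occur while net flux is still outward.
- The correction is unspecified, and under a ratio the reversal disappears.

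That cancellation cannot be relied on either, because nothing in the article says that a ratio is meant.

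**Conclusion.** The contradiction is real and sits in the definition behind a primary endpoint. As written, a-jD for lactate, glucose and oxygen has the opposite sign to its name and to the convention in the Introduction.

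The size is a change of sign with no change of magnitude, in every paired sample from the 20 patients with a jugular bulb catheter. The consequence is conditional: uptake is labelled outflux, and a shift toward uptake appears as a negative change, if the formula is applied literally and then read with the Introduction. This holds for the uncorrected lactate difference and for a regression-adjusted mean change. It does not hold for a lactate/oxygen ratio.

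The sign result follows from the two definitions alone, and only the illustrative concentrations are assumed. Whether the statistical analysis plan or the analysis code repeats the formula cannot be known from the article. The point should be settled before the sub-study IV data are analysed. It does not call the design, the sampling or the other sub-studies into question.

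**What to change.** In Definitions and calculations, define a-jD as the arterial concentration minus the jugular bulb concentration, for lactate, glucose and oxygen alike. Add that a positive value means net cerebral uptake and a negative value net release. This agrees with the variable's name, the Abstract and the Introduction, so nothing else in the article needs to change on this point.

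Then check the analysis code against the corrected line, and the statistical analysis plan too if it repeats the definition. A simple test is that the oxygen difference should come out positive for a brain that consumes oxygen.

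The cost is one line of text and a short code check. No new data, extra sampling or change to patient care is needed.

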### Study endpoints

#### Primary endpoints

Sub-study I: Change in mRS from preoperative assessment to 30 days after surgery, in patients with and without hyperlactatemia.

Sub-study II: Prevalence of hyperlactatemia (defined as at least one measurement of S-lactate> 2.2 mmol / L).

Sub-study III: Association between preoperative and/or intraoperative glucocorticoid treatment, HbA1c and pre-/ postoperative insulin resistance (measured by HOMA-IR), adjusted for hours after surgery.

Sub-study IV: Perioperative change in a-jD (lactate) corrected for change in a-jD (O_2_) from first to last measurement.

#### Secondary endpoints

Sub-study I:

Length of hospital stay, from day of surgery to discharge, in days.Mortality at 30 days, 6 months, 1 year and 5 years (6 months, 1 year and 5 years mortality will not be included in the initial data analysis and publication).

Sub-study II:

Association between pre- / intraoperative risk factors (specified in exploratory endpoints) and hyperlactatemia.

#### Exploratory endpoints

Tumor type, location and estimated volume on preoperative MRI scan.BMI and comorbidity (Charlson Comorbidity Index), with focus on insulin dependent or non-dependent diabetes mellitus type 1 or 2 and liver / kidney disease.Neurological deficits at admission and at discharge. The deficits are assessed by the admitting and discharging clinician through standard neurological examination (mental status, cranial nerves, motor system, reflexes, sensation, and cerebellar function).Preoperative chemotherapy, radiation, or immunotherapy.Dose and duration of pre-, intra-, and post-operative treatment with glucocorticoids (expressed as cortisol equivalents in mg).Surgery duration (minutes) and surgery events (such as other procedures during the surgery and complications, using Landriel Ibañez classification).Position during surgeryComplete or incomplete total resection of tumor, as indicated by the neurosurgeon in the operative report.Type of anesthesia: total intravenous anesthesia, inhalation anesthesia, awake craniotomy.Intra- and post-operative hypotension (defined as MAP < 60 for > 15 min or MAP < 30% of preoperative resting MAP for > 15 min) and treatment with vasopressors (ephedrine, noradrenaline, methoxyarene) in mg for total surgery duration.Perioperative fluid therapy volume and type, as well as total urine output in mL / hour during surgery and in the Post Anesthesia Recovery Unit.Estimated blood loss and blood transfusion volume.Perioperative blood gas parameters: pH, glucose, PaO_2_, PaCO_2_, Base Excess, Hb, HCO_3_, Na, K, Cl.Postoperative nausea, vomiting and pain. Pain assessed by numeric or visual rating scale 0–10.Mobilization time to upright sitting position in the Post Anesthesia Recovery Unit, measured in hours.

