## Bias and confounders

Selection bias is almost always present in studies with voluntary participation. Factors such as socioeconomic status, psychological resilience, severity of illness and number of comorbidities may influence the patient’s readiness to participate. The published data will therefore include the number of non-participants.

Furthermore, patients are included consecutively, in the order in which the studies are mentioned.

Since investigators are susceptible to observational bias, a flowchart and standardized questioning will be used for mRS assessment.

We expect minimal loss to follow-up regarding mortality, as this information will be accessed through the Danish Cause of Death Register. Because many patients may die during the follow-up, survivorship bias is an important type of bias and will be corrected for as appropriate.

The measurement error of S-lactate is expected to be minimal, since all blood samples are analyzed with the same type of equipment.

Major factors influencing lactate production and metabolism are investigated in the study as exploratory endpoints. Continuous variables, such as vital data, are measured on the same type of monitor for all patients. To avoid misclassification, tumors will be classified using the 10^th^ version of International Classification of Disease and the World Health Organization’s classification of tumors, based on the histopathological conclusion from the intraoperative biopsy. The standardized case report form will be publicized as a supplement to study results. Missing data and number of patients lost to follow-up will be reported for each group (normolactatemia and hyperlactatemia) to address any distortion of study results.

We will avoid publication bias by attempting to publish the study irrespective of its conclusions.

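### The relative limb of the hypotension variable is redundant as written: it adds no patient beyond the MAP-below-60 limb unless resting MAP exceeds 200

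*Protocol article*

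**What the plan says.** In the protocol article, Exploratory endpoints includes intra- and postoperative hypotension as a binary condition with two limbs: "MAP < 60 for > 15 min or MAP < 30% of preoperative resting MAP for > 15 min". The first limb is absolute and the second is relative. No unit is printed for either.

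The definition matters beyond description because Secondary endpoints sets this aim for sub-study II: "Association between pre- / intraoperative risk factors (specified in exploratory endpoints) and hyperlactatemia". The intraoperative part of the hypotension variable is therefore a candidate risk factor. The outcome is given in Definitions and calculations: "Hyperlactatemia is defined as the measurement of at least one value of S-lactate > 2.2 mmol / L during the observation period", a period that runs from incision to the end of six hours in the recovery unit.

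The same exploratory list also contains "Perioperative blood gas parameters: pH, glucose, PaO_2_, PaCO_2_, Base Excess, Hb, HCO_3_, Na, K, Cl".

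**The concern.** A two-limb definition of this kind normally exists so that the relative limb can pick up patients whose pressure has dropped well below their own baseline without reaching the absolute cut-off. Here the relative limb is worded as a percentage of the resting value rather than as a fall from it, which puts it far below the absolute cut-off.

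If relative hypotension was meant to count, a patient with a large sustained fall but a MAP at or above 60 is coded as not hypotensive. The reference group then contains patients whom the authors meant to treat as exposed. If that misclassification does not depend on lactate, it would be expected to pull the estimated association between hypotension and hyperlactatemia towards no effect. The protocol's introduction names global or regional ischemia as a known meaning of a raised lactate, so hypotension is a relevant exposure.

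**Working it through.** The plan states no figure on this point, so there is none to reproduce. The check is whether the relative limb can ever classify a patient whom the absolute limb does not.

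**Inputs**
- Absolute limb: MAP below 60 for more than 15 minutes (Exploratory endpoints).
- Relative limb: MAP below 0.30 x R for more than 15 minutes, where R is preoperative resting MAP (same place).
- Connector: "or" (same place).
- R: no distribution is given. A range of 70 to 210 mmHg is assumed, to test the limb.

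**Logic**
If 0.30 x R ≤ 60, every minute below 0.30 x R is also a minute below 60. With the same required duration, any patient who meets the relative limb already meets the absolute one, whether the 15 minutes are counted as continuous or cumulative, provided that both limbs are counted alike. The relative limb can add a patient only if

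0.30 x R > 60, so R > 60 / 0.30 = 200.

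**Relative threshold as printed**

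| Resting MAP R | 0.30 x R | Can add a patient beyond MAP < 60? |
|---|---|---|
| 70 | 21 | no |
| 80 | 24 | no |
| 90 | 27 | no |
| 100 | 30 | no |
| 120 | 36 | no |
| 150 | 45 | no |
| 200 | 60 | no |
| 210 | 63 | yes |

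**Comparison with the other possible reading**
This only shows that the two readings differ; it does not say which was intended. If the limb meant a fall of more than 30%, the threshold would be 0.70 x R, and the limb would add patients whenever R > 60 / 0.70 = 85.7. At R = 80 the threshold is 56, so nothing is added. At R = 90 it is 63 and at R = 100 it is 70. A patient with R = 100 and a sustained MAP from 60 up to 70 would be hypotensive under that reading and is not under the printed one.

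The number of patients reclassified is the number with a sustained MAP at or above 60 but below 0.70 x R. It cannot be computed without the distributions of resting and intraoperative MAP, which the protocol does not report.

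**The case against.** The best defence is that little is at stake. This is one definition within one item of a long exploratory list. None of the stated hypotheses concerns hypotension; they centre on glucocorticoid dose, tumor size, insulin resistance and hyperglycemia. The protocol records invasive and non-invasive blood pressure from the monitors, so the variable can be recoded without loss of data. Any count of missed patients rests on an assumed resting MAP and an assumed intention, and even the fall-based reading adds nobody at or below a resting MAP of about 85.7. All of this stands and limits the size of the point. It does not make the printed limb functional.

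A reader might infer more from the same list: that pH, base excess and bicarbonate are wrong entries because they are consequences of lactate and will enter the regression as false risk factors. The protocol does not establish this. Sub-study II takes only pre- and intraoperative risk factors from a mixed list that also holds deficits at discharge, postoperative nausea and pain, and time to mobilization, so a subset must be meant. The Bias and confounders section says "Major factors influencing lactate production and metabolism are investigated in the study as exploratory endpoints", which does not make every exploratory endpoint such a factor. No section places these three variables in the model, and the covariate set may be fixed in the analysis plan, which is not at hand. Calling all three consequences of lactate is also too absolute: a value at incision can precede a lactate rise, and pH depends on PaCO2 as well. Excluding variables merely because they come from the same samples would also remove glucose, which belongs to the protocol's own hypothesis. What remains is a caution about timing.

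A reader might also object that patients already above 2.2 mmol/L at incision count as cases, although intraoperative factors cannot have caused that. This is true of the binary outcome. But the protocol gives no number of such patients, and it defines a lactate excess that subtracts the incision value to isolate the perioperative contribution. The issue is therefore partly met and is not pressed here.

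**Conclusion.** The hypotension definition is wrong as written. Its relative limb identifies no patient whom the absolute limb misses unless resting MAP exceeds 200, so the candidate risk factor in sub-study II is in effect MAP below 60 for more than 15 minutes. This follows from the printed text and assumes only that both limbs are in the same unit (mmHg) and that duration is counted alike in both. To say that the limb can never add a case would be slightly too strong, but the exception has no practical weight.

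The consequence is modest: possible misclassification of one exposure in a secondary analysis. Its size is unknown, because it depends on the intended rule and on resting pressures that the protocol does not give. The remark on pH, base excess and bicarbonate is a caution about interpretation, not a demonstrated error.

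**What to change.** Before the stored monitor data are coded, the sponsor should reconcile the relative limb with its intended meaning. The definition should state whether a level or a fall relative to resting MAP was meant, and give the unit; otherwise the limb should be deleted and the variable described as an absolute criterion only. Which reading is right is for the sponsor to settle, and no threshold is proposed here. The choice should be made without reference to the lactate results.

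The cost is one corrected sentence and the coding of blood pressure data already being collected. A relative limb also needs each patient's preoperative resting MAP, which the present definition already presupposes.

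As a precaution, report pH, base excess and bicarbonate descriptively, and do not interpret them as risk factors for hyperlactatemia unless the value used was measured before lactate rose. This needs no additional data.

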An observational study design makes it possible to address multiple possible risk factors at once, which is a necessary approach when investigating a multifactorial phenomenon [24], such as hyperlactatemia. Many risk factors, however, may interact with each other. An example of this is the interaction between tumor volume and glucocorticoid dose. Tumor cells produce lactate, a process known as the Warburg effect [25]. A large tumor load may therefore contribute to elevated lactate levels [26]. Furthermore, voluminous and infiltrating brain tumors bring about peritumoral edema with increased intracranial pressure, a condition that is typically remedied with high-dose glucocorticoids, a drug class which may raise lactate through insulin resistance with hyperglycemia [27]. Tumor volume and glucocorticoids are thus interacting risk factors that contribute to lactate production through different mechanisms.

Moreover, lactate production by the tumor itself may be notably higher in patients with brain metastasis and extracranial primary tumors. We expect that these patients will exhibit higher initial lactate levels, but an unchanged "pure" perioperative contribution to the lactate load (see “Definitions and calculations”). Conversely, we expect that initial lactate levels are lower in patients who have received preoperative chemotherapy, radiation or immunotherapy, due to a reduction in tumor burden.

Brain tumors are very diverse, but it is unknown whether the lactate profile and time course differs by tumor type. We have chosen to include patients with meningiomas in our study, as they are classified as brain tumors by the American Association of Neurological Surgeons, and because previous studies have reported on the occurrence of hyperlactatemia even in patients with this tumor type. In the future, it also will be interesting to assess the effect of craniotomy on hyperlactatemia in patients with other surgical (e.g. neurovascular) indications.

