While observational studies may be helpful at recognizing associations between variables, they are not designed to study causality. This study may thus help uncover associations between hyperlactatemia and potential risk factors, which subsequently will need further scrutiny to suggest potential causality. We therefore hypothesize that glucocorticoid-induced insulin resistance is a major risk factor of hyperlactatemia, i.e. that there is an association between glucocorticoid doses, markers of insulin resistance, and arterial lactate levels. If this hypothesis appears to be corroborated and if hyperlactatemia appears to be an independent risk factor of functional outcome, a randomized trial of two different doses of perioperative glucocorticoid may be planned.

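### Sub-study II draws its candidate risk factors for hyperlactatemia from a list that includes glucose (an intermediate) and pH, base excess and HCO3 (partly consequences of lactate); entering them jointly would attenuate the glucocorticoid association

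*Protocol article*

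**What the plan says.** Under Secondary endpoints, the sub-study II analysis is defined by cross-reference: "Association between pre- / intraoperative risk factors (specified in exploratory endpoints) and hyperlactatemia". The only list this can mean is under Exploratory endpoints. There the exposure of main interest, "Dose and duration of pre-, intra-, and post-operative treatment with glucocorticoids (expressed as cortisol equivalents in mg", stands in the same list as "Perioperative blood gas parameters: pH, glucose, PaO_2_, PaCO_2_, Base Excess, Hb, HCO_3". No time point is attached to the blood gas values.

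The Abstract names the method: "Multivariate logistic regression will be used to identify risk factors for hyperlactatemia". The Statistical analysis section pairs logistic regression with binary variables but names no covariates and no selection rule. Bias and confounders describes the exploratory items as covering the main influences on lactate.

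On mechanism, the Introduction says that high glucose can itself induce hyperlactatemia. The Discussion describes glucocorticoids as "a drug class which may raise lactate through insulin resistance with hyperglycemia" and states the working hypothesis as "there is an association between glucocorticoid doses, markers of insulin resistance, and arterial lactate levels".

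**The concern.** The cross-reference sorts candidates by timing (before or during surgery) and not by their role relative to lactate. Three kinds of variable therefore sit in one candidate set.

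- Upstream factors: glucocorticoid dose, tumor volume, comorbidity.
- An intermediate: glucose, which the article places between glucocorticoid and lactate.
- Likely consequences: pH, base excess and HCO3, which tend to fall as lactate accumulates.

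A glucocorticoid coefficient adjusted for glucose describes only the part of the association that does not run through glucose. Adjusting for consequences of the outcome distorts the coefficient further. A low base excess listed as a risk factor for high lactate would be close to restating the outcome.

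Sub-study II is the only named endpoint that relates glucocorticoid dose to hyperlactatemia in all 450 patients. The Discussion says that a randomized comparison of glucocorticoid doses may follow if the hypothesis is supported and if hyperlactatemia also appears to be an independent risk factor for functional outcome. An attenuated estimate could weigh on that decision.

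**Working it through.** **No plan figure to reproduce.** The article gives no effect size or power for sub-study II. Its one sample size, 450, was derived from rates of new neurological deficits and serves below only as the number of patients.

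**Step 1: the passages side by side.**
- Outcome window (Definitions and calculations): any S-lactate above 2.2 mmol/L from surgical incision to the end of 6 hours in the recovery unit.
- Sampling (Intraoperative data collection): hourly from skin incision. Intraoperative blood gas values thus fall inside the outcome window, and limiting candidates to pre- and intraoperative factors does not exclude them.
- Glucose: on the path from glucocorticoid to lactate, by the Introduction and the Discussion.
- pH, base excess, HCO3: the article does not call them consequences of lactate. That is general physiology, and they also depend on PaCO2 and fluids.

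**Step 2: size if the variables enter jointly (N = 450).** All path strengths are assumptions. Variables are standardized: S is glucocorticoid dose, G glucose, L lactate, e independent noise.
- G = a·S + √(1 − a²)·e
- L = b·G + c·S + noise with variance 1 − b² − c² − 2abc
- Base excess = −0.6·L + 0.8·e; HCO3 = −0.5·L + 0.87·e
- Hyperlactatemia = L above 0, so prevalence is 50% (the Introduction reports 32–68%)
- Total effect = ab + c; mediated share = ab/(ab + c)

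Mediated shares:
- 0.25/0.25 = 100%
- 0.20/0.30 = 67%
- 0.12/0.27 = 44%
- 0.09/0.29 = 31%

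Odds ratio per SD of dose, with the percentage of 400 simulated studies giving P < 0.05:

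| a, b, c | Mediated | Dose only | + glucose | + base excess, HCO3 | + all three |
|---|---|---|---|---|---|
| 0.5, 0.5, 0 | 100% | 1.53 (99%) | 1.00 (4%) | 1.39 (81%) | 0.99 (4%) |
| 0.5, 0.4, 0.1 | 67% | 1.67 (100%) | 1.21 (34%) | 1.51 (92%) | 1.17 (21%) |
| 0.4, 0.3, 0.15 | 44% | 1.58 (99%) | 1.31 (70%) | 1.45 (89%) | 1.25 (39%) |
| 0.3, 0.3, 0.2 | 31% | 1.65 (100%) | 1.45 (93%) | 1.48 (89%) | 1.33 (64%) |

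Simulation error on a percentage near 39% is √(0.39 × 0.61/400) = 0.024, or about 2 points.

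**Step 3: a second set of assumptions.**
- Inputs: log-lactate with total effect 0.12 per SD of dose and residual SD 0.4; dose–glucose correlation 0.4; about 46% hyperlactatemia; base excess falling 0.9 per mmol/L lactate with noise SD 1 to 2; 400,000 simulated patients.
- Unadjusted odds ratio: about 1.5 to 1.6.
- With glucose: about 1.28, 1.13 and 1.00 at 50%, 75% and 100% mediation.
- With base excess alone: 1.58 falls to between 1.44 and about 1.54.

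Both sets agree. Glucose does most of the damage where mediation is substantial, the association vanishes only at full mediation, and acid-base variables alone attenuate it modestly. pH was not simulated.

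**The case against.** The strongest reply is that the article specifies no such model. It names a regression type, gives no covariate set, and promises a public statistical analysis plan, where covariate choice normally belongs. Nor is the exploratory list literally a covariate list: it includes "Mobilization time to upright sitting position in the Post Anesthesia Recovery Unit, measured in hours", which cannot be a pre- or intraoperative risk factor. The hypothesis is worded as an association, and the Discussion says that observational studies are not designed to study causality. Glucose is a legitimate correlate to report, since the Introduction expects hyperglycemia to be associated with the severity of hyperlactatemia. Sub-study III offers a separate look at glucocorticoids and insulin resistance.

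Much of this stands. A reader might infer that the planned model will remove the glucocorticoid effect. The document does not support that: joint entry is nowhere stated, and complete loss requires that the whole effect run through glucose. Nor does the document say that pH, base excess and HCO3 are purely consequences of lactate.

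What does not stand is that nothing has been fixed. The secondary endpoint itself points to the list as the source of risk factors, and its timing limit leaves intraoperative glucose and acid-base values in. The difficulty does not depend on a causal claim either, because an association with dose given glucose differs from an association with dose. The primary endpoint of sub-study III relates glucocorticoids to HOMA-IR, with insulin resistance markers taken in 100 patients, and so does not replace the dose–lactate analysis in the full cohort.

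**Conclusion.** The point holds conditionally. The article fixes its candidate set badly: an intermediate and likely consequences of the outcome are offered as risk factors beside the exposure of interest. If they enter the multivariable model with glucocorticoid dose, its association is attenuated. Under the assumed paths, an odds ratio of about 1.5 to 1.6 falls to about 1.3 when roughly half the effect runs through glucose, and to 1.0 when all of it does. With 450 patients and 44% mediation, adjusting for glucose, base excess and HCO3 together lowers the chance of a significant dose term from 99% to 39%. These sizes are illustrative, since the article supplies none of the path strengths. The circular labelling of acidosis as a risk factor does not depend on them.

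Severity is moderate. A secondary endpoint of one sub-study is affected; no primary endpoint, sample size or data collection is. It should be settled before the analysis.

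**What to change.** Amend the sub-study II secondary endpoint and the exploratory list it refers to, and carry the same wording into the statistical analysis plan:

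1. State that intraoperative and postoperative pH, base excess and HCO3 are not candidate risk factors. Report them descriptively alongside lactate.
2. Estimate the association of glucocorticoid dose with hyperlactatemia in a model without glucose, adjusted only for named upstream confounders. Tumor volume is an obvious one, since the Discussion links larger tumors to higher glucocorticoid doses.
3. Add glucose in a separate model labelled as a mediator analysis, and present the two dose coefficients side by side.

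The cost is a wording change and one additional model. No new data are needed.
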